## Abstract

**Background:**

In Chile, more than 500 women die every year from cervical cancer, and a majority of Chilean women are not up-to-date with their Papanicolau (Pap) test. Mobile health has great potential in many health areas, particularly in health promotion and prevention. There are no randomized controlled trials in Latin America assessing its use in cervical cancer screening. The ‘Development of Mobile Technologies for the Prevention of Cervical Cancer in Santiago, Chile’ study aims to determine the efficacy of a text-message intervention on Pap test adherence among Chilean women in the metropolitan region of Santiago.

**Methods/design:**

This study is a parallel randomized-controlled trial of 400 Chilean women aged 25–64 who are non-adherent with current recommendations for Pap test screening. Participants will be randomly assigned to (1) a control arm (usual care) or (2) an intervention arm, where text and voice messages containing information and encouragement to undergo screening will be sent to the women. The primary endpoint is completion of a Pap test within 6 months of baseline assessment, as determined by medical record review at community-based clinics. Medical record reviewers will be blinded to randomization arms. The secondary endpoint is an evaluation of the implementation and usability of the text message intervention as a strategy to improve screening adherence.

**Discussion:**

This intervention using mobile technology intends to raise cervical cancer screening adherence and compliance among a Chilean population of low and middle-low socioeconomic status. If successful, this strategy may reduce the incidence of cervical cancer.

**Trial registration:**

Clinicaltrials.gov NCT02376023 Registered 2/17/2015.

First participant enrolled Feb 22nd 2016.

**Electronic supplementary material:**

The online version of this article (10.1186/s12885-017-3870-8) contains supplementary material, which is available to authorized users.

## Background

Cervical cancer is the third leading cause of death of women worldwide. In 2020 more than 315,000 women are estimated to die due to cervical cancer; more than 85% of these deaths will be in developing countries. In 2015, an estimated 88,000 new women were diagnosed with cervical cancer in the Americas, with more than 38,000 deaths estimated that same year [1]. In Chile, more than 500 women die every year from cervical cancer. In Chile, only 59% of the population is up-to-date with their Pap test, and this figure has not changed in the last 10 years [2]. The distribution of cervical cancer, like that of other cancers, follows a pattern of inequality in that women of lowest socioeconomic status are those most affected [3, 4].

Mobile technologies have increased exponentially in the last few years [5]; in 2009, mobile telephones could be found in more than 90% of Chilean homes and were widely distributed across all socioeconomic levels. While inequalities still remain in this area, they are much less profound than with other technologies; its distribution varies between 97% in high SES and 82.8% in low SES [6, 7]. Because of this technological explosion, mobile health (mHealth), or “medical and public health practice supported by mobile devices” [8], has great potential in many health areas such as promotion and prevention [9]. Overall interest in mobile health is widespread. The World Health Organization’s (WHO) report on mHealth in 2011 [8] states that mobile health strategies exist in at least 75% of the countries that belong to the WHO in each region. According to the European Commission in its program “Digital Agenda for Europe”, mHealth has the potential to reduce inequalities regarding the delivery of health services, to empower patients to control their own health, and to improve the cost-effectiveness of health care delivery [10].

There is a lack of evidence supporting mHealth in cancer prevention. Some evidence exists that shows that mobile health is an effective strategy for treatment adherence for prenatal care and those with HIV and tuberculosis [11–14]. In cancer prevention, a study in Botswana described how community workers were trained to use mobile cameras to send images of possible cervical cancer to expert gynecologists located remotely. The study concludes mHealth could be a powerful tool for cervical cancer screening [15]. Nevertheless, there are no reported randomized controlled trails in Latin America of using mobile health technologies in cancer prevention.

The aims of this study are: 1. To ascertain the efficacy of an intervention using mobile technologies on Pap test adherence compared to a control condition; and 2. To evaluate the implementation and usability of this intervention in three health centers of the South East Metropolitan Health District of Santiago, Chile.

## Methods/design

The ‘Development of Mobile Technologies for the Prevention of Cervical Cancer in Santiago, Chile’ or “Messages for your health” is a parallel randomized controlled trial with both a qualitative and quantitative phase. In the qualitative phase, we aimed to acquire information to design a suitable intervention using mobile technologies for our study population. Six focus groups (two in each health center) were carried out with women who received care at eligible health care centers in order to determine the barriers and facilitators to implementing a text message intervention. An additional three focus groups were carried out with midwives at the health care centers in order to characterize the usual care that women receive. (In Chile, midwives are in charge of women’s primary care). This phase was completed in March 2015 and served as basis for the developing the quantitative phase of the actual mHealth intervention. Focus group guides in English and Spanish can be reviewed as Additional file 1.

In the quantitative phase, participants will be randomized into a control/usual care arm or a text message intervention arm (Fig. 1). The messages will educate participants about the importance of cervical cancer screening and encourage them to receive a Pap test. The study is being conducted in La Pintana, Santiago, Chile and has been approved by the Institutional Review Board (IRB) of the Pontificia Universidad Católica de Chile. ID: CEC MED UC 14–213.

**Fig. 1 Fig1:**
[figure not shown]
Study protocol. Participants´ randomization scheme

### Setting

Chile has a universal health coverage system and local community registries in primary health clinics. The study is being conducted in two health care centers located in the district of La Pintana. The municipality of La Pintana is one of 52 municipalities in the metropolitan region of Santiago. Approximately 30% of the population in La Pintana lives below the poverty level, which is a significantly higher rate than the 14.4% of people living in Chile below the poverty level. The average household income in La Pintana is 635 USD. In Chile it is 1100 USD [16].

Originally the study was to be implemented in three health clinics, two health clinics located in the municipality of La Pintana and one health clinic located in the municipality of Puente Alto.

Both La Pintana clinics serve populations with similar demographics and are funded by the state through a capitated model. The mode of administration differs in that the municipality manages one clinic and the other is managed by a private University.

We chose these clinics since there may be differences in adherence given these two different administrators. The Puente Alto clinic was finally excluded because demographics did not align with La Pintana clinics and efforts to recruit participants were not successful.

With the assistance of the clinics’ health care teams, investigators will identify women non-adherent with Pap testing and review medical records at the end of the study to monitor Pap test screening adherence.

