### Randomization

Following baseline assessment, women will be randomized to either the intervention or control arm via a computerized program. Investigators and statisticians will be blinded to the allocation groups.

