#### Control arm

Participants randomized to the control arm (usual care) will not receive any educational or motivational messages or intervention materials from study staff. Usual care consists of any information on Pap tests and cervical cancer risk reduction typically provided by midwives to all women at the clinics. Women can schedule an appointment for their Pap test in person at the clinics. All services at the clinics, including Pap testing, are free. Usual care may vary slightly across the different participating clinics.

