### Sample size

We will estimate adherence probabilities to be approximately 0.30 for the usual care arm and 0.45 for the text message intervention arm. Power calculations are based on a sample size of 176 in each of the two study arms, and assume a 10% attrition. A Chi square test will be carried out to compare compliance between the control arm and the intervention arm. The significance level is aimed at 0.05 with a power of 80%.

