### Statistical analysis

Pap test adherence will be coded as a binary variable. The intervention will be evaluated based only on Pap test completion at six months after the baseline survey date. Chi square tests of 2 X 2 tables (compliance Yes/No by arm Control vs Text Message Intervention) will be used to determine if the intervention affects the probability of Pap test compliance at follow-up. An expected 400 women (200 per arm to each of 2 arms; control, text message intervention) will be randomized into the study, which will accommodate a 10% loss to follow-up.

We will adjust for age, socioeconomic class, number of children and other relevant demographic and clinical variables.

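### The clinics were chosen because adherence may differ between them, but the pooled primary chi-square and the named covariates leave clinic out, at a small cost in precision

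*Protocol article*

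**What the plan says.** All references are to the protocol article.

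- **Setting** gives the reason for using these two La Pintana clinics: "We chose these clinics since there may be differences in adherence given these two different administrators". One is run by the municipality and the other by a private university. The same section describes their populations as demographically similar.
- **Control arm** allows the comparator to differ by site: "Usual care may vary slightly across the different participating clinics".
- **Randomization** says that "women will be randomized to either the intervention or control arm via a computerized program". No stratum or block is mentioned and none is ruled out. The figure with the randomisation scheme is not available in the text reviewed.
- **Sample size** and **Statistical analysis** fix the primary comparison as a chi-square test on compliance (yes/no) by arm, with no clinic term.
- **Statistical analysis** then adds: "We will adjust for age, socioeconomic class, number of children and other relevant demographic and clinical variables". Clinic is not named, and the list is left open.

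**The concern.** The investigators single out one factor, the clinic, as a possible source of variation in the primary outcome. The test they then fix does not use it, and neither do the three covariates they name. Demographic covariates are unlikely to stand in for clinic, because the Setting section describes the two populations as similar.

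What is at stake depends on how the women were randomised:

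- **Not stratified by clinic:** the clinic mix can differ between arms by chance. This adds noise to the arm difference that a stratified test would remove.
- **Stratified by clinic:** the pooled test uses a standard error that is too large, so it rejects less often than the nominal 5%.

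In both cases the trial gives up some precision that a variable known for every woman would recover.

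**Working it through.** **1. The plan's own sample size.** Inputs from the Sample size section: "We will estimate adherence probabilities to be approximately 0.30 for the usual care arm and 0.45 for the text message intervention arm"; significance level 0.05 (two-sided assumed, as the side is not stated); power 80%; and "Power calculations are based on a sample size of 176 in each of the two study arms, and assume a 10% attrition".

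- Without continuity correction: n = [1.96 x sqrt(2 x 0.375 x 0.625) + 0.842 x sqrt(0.30 x 0.70 + 0.45 x 0.55)]^2 / 0.15^2 = 162.3, so 163 per arm.
- With continuity correction: n' = (162.3/4) x [1 + sqrt(1 + 4/(162.3 x 0.15))]^2 = 175.4, so **176 per arm**, as stated.
- Attrition: 176/0.90 = 195.6, so 196 per arm. The plan's 200 per arm covers this and leaves 200 x 0.90 = 180 evaluable.

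The stated figure reproduces, and leaving clinic out does not disturb it.

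**2. Assumptions for the clinic effect.** The article gives neither the size of a clinic difference nor the split of women between clinics. Assumed: two clinics of equal size, 180 evaluable women per arm, overall rates held at 30% and 45%, and the same odds ratio in both clinics. The clinic gap in control-arm completion is varied over 0, 10, 20 and 30 percentage points.

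**3. Chance imbalance under simple randomisation.** The SD of the between-arm difference in clinic share is sqrt(2 x 0.25/180) = 0.0527, or 5.3 points. The resulting shift in the arm difference has a 95% range of ±1.96 x gap x 0.0527:

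- gap 10: ±1.0 point
- gap 20: ±2.1 points
- gap 30: ±3.1 points

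The planned effect is 15 points.

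**4. Power and type I error under simple randomisation.** Simulation with 100,000 runs per case, pooled chi-square (without continuity correction) against the Cochran-Mantel-Haenszel (CMH) test stratified by clinic:

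| Clinic gap (points) | Power, pooled | Power, CMH | Difference (points) | Type I error, pooled |
|---|---|---|---|---|
| 0 | 84.0% | 83.8% | -0.2 | 5.1% |
| 10 | 84.3% | 84.6% | 0.3 | 5.1% |
| 20 | 84.1% | 85.8% | 1.7 | 5.2% |
| 30 | 83.9% | 88.1% | 4.2 | 5.1% |

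The Monte Carlo standard error of each power figure is sqrt(0.84 x 0.16/100,000) = 0.0012, about 0.1 point. Repeated simulations agreed to within a few tenths of a point.

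**5. Type I error of the pooled test if randomisation was stratified by clinic.** At a common rate of 30%, the pooled test uses a variance proportional to 0.30 x 0.70 = 0.21. With clinic balanced by design, the true variance is proportional to 0.21 - gap^2/4. The actual type I error is 2 x [1 - Φ(1.96/sqrt(ratio))], where ratio is the true variance divided by 0.21:

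- gap 10: ratio 0.2075/0.21 = 0.988, type I error 4.9%
- gap 20: ratio 0.2000/0.21 = 0.952, type I error 4.5%
- gap 30: ratio 0.1875/0.21 = 0.893, type I error 3.8%

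Simulation gives 4.4% to 4.5% at a gap of 20 and 3.8% to 3.9% at a gap of 30.

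**The case against.** The strongest case on the other side has four parts.

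- **An unadjusted chi-square is a valid primary test in an individually randomised trial.** This stands. Pooled type I error stays at 5.1% to 5.2% under simple randomisation. Chance imbalance of clinic is random error that the test already allows for, not bias.
- **The article never says that randomisation ignores clinic.** This stands. A reader might infer from the Randomization section that clinic is not a stratum, but that would be reading silence as a statement. A condensed article often leaves strata to the full protocol, and the scheme figure is not available.
- **The article does not claim a large clinic difference.** This also stands. It says only that adherence may differ and that usual care may vary slightly. A reader might take clinic to be a strong predictor, but no figure supports that. At a gap of 10 points the gain from stratifying is negligible, and the gaps of 20 and 30 are assumptions.
- **The covariate list is open, so clinic may enter later.** This stands in part. Clinic is not excluded, but it is not plainly a demographic or clinical variable. Bringing it in through an open phrase would leave the choice until after the data are seen. The adjustment sentence also does not alter the pooled chi-square described before it.

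Nor do the study aims include a comparison of clinics, so choosing sites that may differ does not by itself oblige a stratified test. What remains is that the article does specify a test and does name covariates, and both omit the one factor on which it bases the choice of sites.

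**Conclusion.** The point holds as a modest matter of efficiency and consistency. The pooled chi-square is valid under simple randomisation, and the 176 evaluable and 200 randomised per arm are unaffected. Pooled power stays near 84% at every gap examined, above the planned 80%.

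The loss against a clinic-stratified test is about 0 points of power at a clinic gap of 0 to 10 points, 2 at 20 and 4 at 30. If randomisation was stratified by clinic, the pooled test is conservative, with type I error of about 4.4% at a gap of 20 and 3.8% at 30. These sizes rest on equal clinics, 180 evaluable women per arm, a common odds ratio and overall rates of 30% and 45%. The clinic gap itself is unknown.

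The documents do not support a claim of bias, of an undersized trial, or of unstratified randomisation.

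**What to change.** Before unblinding:

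- Make the primary test a Cochran-Mantel-Haenszel test stratified by clinic, or add clinic as a fixed term in the primary model.
- Name clinic explicitly, so that it does not depend on the open end of the covariate list.
- State whether randomisation was stratified by clinic.
- Report the arm difference within each clinic descriptively. Do not attribute a clinic difference to the type of administrator: there is one clinic per administrator, so the two cannot be separated.

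The cost is a short analysis amendment, needed because enrolment began in February 2016. No new data are required, since each woman is enrolled at one of the two centres. If the clinics do not differ, the stratified test costs about 0.1 to 0.2 points of power. Neither the randomisation nor the sample size needs to change.

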### Participants

The study aims to recruit 400 women who will be enrolled at one of the two participating health care centers. Participating women will be non-adherent with current Chilean recommendations for Pap test screening (they will not have a Pap test within the past 3 years). Eligible women will be between 25 and 64 years of age with no prior history of cervical cancer. Participants must own and use a mobile phone, be free from any mental or physical disabilities that inhibit them from understanding the implications of the study or being able to reach the health clinic for an exam, and cannot be considering relocating within the next year.

### Recruitment of participants

Computerized patient records will be used to obtain basic patient information of women who receive care at the two participating health care centers.

All non-adherent, eligible women registered in the clinic will be appropriate to participate in this study. Those agreeing to participate will be included until we have reached the estimated sample size of 400 participants. Women will be reached by a community health worker at their house or by phone.

Those interested in participating will be told they will be randomized to an intervention arm or a control arm in the project. The community health worker will ask the women to sign an informed consent to participate in the study. Once consent is obtained, the participant will complete a baseline survey. The baseline questionnaire includes items on cervical cancer screening knowledge and attitudes, sociodemographic variables, and cellphone use. Women will receive an estimated 4USD charge in their cell phones as incentive to keep their phone number for as long as the intervention lasts.

### Randomization

Following baseline assessment, women will be randomized to either the intervention or control arm via a computerized program. Investigators and statisticians will be blinded to the allocation groups.

#### Control arm

Participants randomized to the control arm (usual care) will not receive any educational or motivational messages or intervention materials from study staff. Usual care consists of any information on Pap tests and cervical cancer risk reduction typically provided by midwives to all women at the clinics. Women can schedule an appointment for their Pap test in person at the clinics. All services at the clinics, including Pap testing, are free. Usual care may vary slightly across the different participating clinics.

#### mHealth intervention

We chose Nexmo ® as the platform to deliver the mHealth messages given its reliability and low cost. Participants will be sent messages containing information and encouragement to undergo cervical cancer screening. Information will also be provided about health clinic hours and locations. Information and motivational text messages will be delivered twice a week for four months followed by two months of voice messages also twice a week, with the same information. As noted above, specific content, frequency, and message modality (text vs voice message) was determined according to the results of the focus groups and participants’ preferences.

### Primary outcome

The primary outcome is the completion of a Pap test within 6 months of baseline assessment. Participants will be tracked via medical record review as well as through the national database for Pap registry. The difference in Pap testing rate between control and intervention arms will be determined.

### Secondary outcomes

We will assess implementation and usability of a text message intervention by estimating the number of messages sent and received, the answering rate to the voice calls and the stability and reliability of the platform chosen.

### Sample size

We will estimate adherence probabilities to be approximately 0.30 for the usual care arm and 0.45 for the text message intervention arm. Power calculations are based on a sample size of 176 in each of the two study arms, and assume a 10% attrition. A Chi square test will be carried out to compare compliance between the control arm and the intervention arm. The significance level is aimed at 0.05 with a power of 80%.

### Statistical analysis

Pap test adherence will be coded as a binary variable. The intervention will be evaluated based only on Pap test completion at six months after the baseline survey date. Chi square tests of 2 X 2 tables (compliance Yes/No by arm Control vs Text Message Intervention) will be used to determine if the intervention affects the probability of Pap test compliance at follow-up. An expected 400 women (200 per arm to each of 2 arms; control, text message intervention) will be randomized into the study, which will accommodate a 10% loss to follow-up.

We will adjust for age, socioeconomic class, number of children and other relevant demographic and clinical variables.

## Discussion

Cervical cancer screening is a national priority in Chile. Even with free screening nationwide and a cervical cancer screening registry, more than 40% of eligible women do not adhere to cancer screening guidelines. Mobile technologies have permeated widely in Latin America and in Chile but there are no randomized control trials described using these technologies for cancer screening locally.

The ‘Development of Mobile Technologies for the Prevention of Cervical Cancer in Santiago, Chile’ study has the potential to evaluate mobile health as a means to reduce disparities in the incidence of cervical cancer through promoting Pap test adherence to increase early detection. The results of this study will hopefully increase Pap adherence of low SES Chilean women. Determining the effect of an mHealth intervention on screening adherence among low SES Chilean women who are non-adherent with current recommendations for Pap test screening may help with increasing rates of screening adherence nationally. If effective, an mHealth intervention strategy may serve as a means of reducing cervical cancer morbidity and mortality, and could possible be applied to the prevention of other diseases.

